#### 2.4.3. Randomization and blinding.

Following the completion of the run-in period, eligible participants will be randomized in a 1:1 ratio to either the intervention or the control group. Randomized allocation sequences will be generated using a permuted block design in R software. Sequentially numbered, opaque, sealed envelopes will be prepared and stored by a non-investigational team member. To minimize selection bias, the randomization codes are assigned by an independent researcher. Once an eligible participant is enrolled, the principal investigator notifies the independent researcher to open sequentially the sealed envelope for allocation. yFMT and placebo capsules are identical in appearance, shape, odor, and specifications.

The investigational capsules will be assigned predefined random codes that were dispensed without selection. Randomization number is not allowed to be reassigned following participant discontinuation. The randomization code will be securely maintained by an independent statistician throughout the study. The code will remain inaccessible to investigators, participants, and endpoint assessors, except for authorized access by the independent Data Monitoring Committee (DMC) during the pre-specified interim analysis. Full unblinding will occur only after database lock and completion of the final analysis.

#### 2.4.4. Study intervention.

(1) Regimen: The yFMT capsules are manufactured by Meiyitian Biomedical Co., Ltd. (Wuhan, Hubei, China) and prepared from rigorously screened healthy young donors (aged 4–17 years), selected for the relatively high temporal stability of the gut microbiota during this developmental window [19,20]. Donor-recipient matching follows a three-dimensional framework based on disease state, sex, and age (Fig 3). All donor screening, infectious disease testing, and microbiological safety procedures comply with the Chinese expert consensus on FMT donor management [21], with dual informed consent obtained from both donors (when age-appropriate) and their legal guardians. Eligible participants will be randomized to receive either yFMT capsules or identical capsules (skimmed milk and starch). The administration protocol is as follows: 6 capsules are to be taken orally twice daily (a total of 12 capsules/day) under fasting conditions (at least 2 hours before or after meals) for six consecutive days, delivering a total cumulative dose of approximately 2.0 × 10^^^ [13] viable bacteria per course [22]. All capsules must be swallowed whole without chewing to maintain bacterial viability and blinding. All participants maintain their usual insulin therapy throughout the study period and are allowed to adjust their insulin dose based on CGM data.(2) Storage and Handling: Capsules are stored at −80°C and must be administered within 20 minutes of thawing.(3) Safety Monitoring: During the 6-day intervention period, participants will be monitored daily for:a. Gastrointestinal tolerance: specifically assessing bloating, abdominal pain, changes in bowel habits (constipation or diarrhea), nausea, or vomiting.b. Systemic symptoms: fever, rash, or any new allergic-like reactions.c. Glucose metabolism: close review of CGM data for significant or unexplained glycemic fluctuations, particularly hypoglycemia.

**Fig 3 pone.0343078.g003:**
[figure not shown]
Source and allocation of gut microbiota capsules. Abbreviations: yFMT, youth-derived fecal microbiota transplantation; T1DM, Type 1 diabetes mellitus; TIR, Time in Range; TBR3.9, Time Below Range <3.9mmol/L;.

Any adverse events (AEs) will be recorded, and their relationship to the study intervention will be assessed using a predefined causality algorithm specific to microbiota-based therapies.

#### 2.4.5. Follow-up visits.

(1) Interim Visit (Week 4 ± 3 days, outpatient): Includes clinical evaluation, laboratory tests (metabolic, β-cell function, immune markers), CGM data collection (Weeks 2–4), PROs, and AEs/Serious adverse events (SAEs) documentation.(2) Final Visit (Week 12 ± 3 days, outpatient): A comprehensive reassessment, including all parameters from the interim visit plus final gut microbiome and safety laboratory samples. CGM data from Weeks 10–12 are collected. The study concludes with database lock and unblinding.

A detailed schedule is provided in Table 2.

**Table 2 pone.0343078.t002:** Study visit schedule.

Process	Screening period	Run-in period 1	Baseline period	Run-in period 2	Intervention period	Mid-term follow-up	Final follow-up
	Day −17	Day −17 to Day −3	Day −3	Day −3 to Day 0	Day 0 to Day 6	Week 4 ± 3 days	Week 12 ± 3 days
Obtain informed consent	**√**						
Basic characteristics	**√**						
Lifestyle survey			**√**				
Record anthropometric measurements			**√**			**√**	**√**
Average total daily insulin dose (Past 1–2 Weeks)			**√**			**√**	**√**
Glucose + C-peptide (Fasting and MMT 2h)			**√**			**√**	**√**
HbA1c	**√**		**√**			**√**	**√**
Islet autoantibody titer			**√**			**√**	**√**
Treg/Th17 ratio			**√**			**√**	**√**
Lipids profile			**√**			**√**	**√**
Liver function			**√**				**√**
Renal function			**√**				**√**
Thyroid function			**√**				**√**
Infection markers and inflammatory cytokines			**√**			**√**	**√**
Intestinal Barrier-Related Antibodies			**√**			**√**	**√**
Safety assessments			**√**		**√**	**√**	**√**
AEs and SAEs			**√**			**√**	**√**
Gut microbiome			**√**			**√**	**√**
Serum metabolomics			**√**				**√**
Bowel cleansing				**√**			
Oral yFMT capsules					**√**		
Standard insulin therapy		**√**	**√**	**√**	**√**	**√**	**√**
CGM monitoring		**√**			**√**	**√**	**√**
Questionnaires			**√**			**√**	**√**
Feasibility endpoints							**√**
Provision of yFMT to the placebo group after unblinding							**√**

**Note:** Basic characteristics: age, sex, ethnicity, height, weight, waist circumference, hip circumference, duration of T1DM, past medical history, and medication history; Lifestyle survey: smoking, alcohol consumption, diet, and physical activity; Record anthropometric measurements: height, weight, blood pressure, pulse, waist circumference, hip circumference, BMI, and WHR; Infection markers: WBC, ESR, hs-CRP, PCT; cytokines: TNF-α, IL-1β, IL-8, IFN-γ; Intestinal Barrier-Related Antibodies: Anti-LPS, Anti-Occludin Antibodies; Safety assessments: body temperature, pulse, respiration, and blood pressure; Adverse events and serious adverse events: including abnormalities in liver and kidney function tests, as well as symptoms such as nausea, abdominal pain, diarrhea, abdominal distension, fatigue, constipation, loss of appetite, and allergic reactions. SAEs refer to medical events occurring during the clinical trial that result in hospitalization or prolonged hospitalization, disability, impaired work capacity, life-threatening conditions, death, or congenital malformations; Completion of relevant questionnaires: Simplified Chinese version (Mainland China) of the EQ-5D-5L scale, Chinese version of the Hypoglycemia Fear Survey-Worry Subscale (HFS-WS), and the Diabetes Distress Scale (DDS). Feasibility endpoints: Recruitment rate, Retention rate, Intervention adherence, Acceptability.

**Abbreviations:** MMT 2h, Mixed-Meal Tolerance Test, 2 hours; HbA1c, glycated hemoglobin; Treg, Regulatory T cell; Th17, T helper 17 cells; yFMT, youth-derived Fecal Microbiota Transplantation; CGM, Continuous Glucose Monitoring; T1DM, Type 1 Diabetes Mellitus; BMI, Body Mass Index; WHR, Waist-to-Hip Ratio; WBC, White Blood Cell; ESR, Erythrocyte Sedimentation Rate; hs-CRP, High-Sensitivity C-reactive Protein; PCT, Procalcitonin; TNF-α, Tumor Necrosis Factor-alpha; IL-1β, Interleukin-1β; IL-8, Interleukin-8; IFN-γ, Interferon gamma; Anti-LPS, Anti-Lipopolysaccharide Antibody.

#### 2.4.6. Post-study procedures.

To ensure ethical equity, all consenting participants in the placebo group will be eligible to receive a complimentary course of open-label yFMT upon study unblinding, regardless of baseline glycemic status. This extension phase utilizes a treatment regimen and dose identical to those of the yFMT group. Data from this open-label extension phase will be analyzed separately and are not included in the primary analysis. Post-treatment, participants are advised to undergo HbA1c testing and 14-day CGM monitoring at 1 and 3 months. Concurrently, they are instructed to self-report any subsequent adverse events via the 24-hour safety hotline.

#### 2.4.7. Strategies to enhance feasibility and adherence.

To ensure successful recruitment, retention, and protocol adherence, the following strategies will be implemented. Recruitment: Potential participants will be identified through the established T1DM cohort at our center, supplemented by community referrals and social-media-based patient community recommendations. Study information will be disseminated through posters, WeChat official accounts, and direct mailings to registered patients. Retention and Adherence: (1) All study-related clinical assessments and laboratory tests are provided free of charge to participants; (2) participants will receive reminder calls and WeChat messages before each scheduled visit; (3) flexible rescheduling within the ± 3-day window is permitted; and (4) participants can communicate directly with the study coordinator via WeChat for real-time queries and support. Intervention Adherence: During the 6-day inpatient intervention period, study nurses will directly observe each capsule administration. During the outpatient follow-up phase, adherence will be monitored by counting returned capsules and recorded in the case report form. These measures are designed to minimize missing data and ensure the feasibility of this pilot trial.

### 2.5. Endpoints

The primary endpoint is change in the composite achievement rate of TIR > 70% and TBR3.9 < 4% at 3 months (Weeks 10–12) post-intervention compared to baseline (days −17 to −3 during the run-in period). Secondary efficacy endpoints included glycemic metabolism, β-cell function, insulin sensitivity, immunomodulation, Intestinal Barrier-Related Antibodies, inflammatory markers, gut microbiome and metabolites, PROs, lipid profile and TDD. The 1-month (Weeks 2–4) assessment is defined as a secondary endpoint to evaluate early glycemic changes. Feasibility endpoints include: (1) recruitment rate (proportion of screened participants enrolled); (2) retention rate (proportion of participants completing the 12-week follow-up); (3) intervention adherence (percentage of prescribed capsules consumed); and (4) acceptability (participant-reported tolerability and willingness to undergo treatment). Safety endpoints comprised the incidence of AEs (such as gastrointestinal symptoms, infection-related events, immune-related reactions, and allergic responses), as well as the incidence of serious AEs (SAEs, including severe hypoglycemia, diabetic ketoacidosis, hospitalization, disability, life-threatening events, or death). Detailed information is provided in Table 3.

**Table 3 pone.0343078.t003:** Study endpoints.

Primary endpoint	change in the composite achievement rate (TIR > 70% and TBR3.9 < 4%) at 3 months (Weeks 10–12) post-intervention
**Secondary endpoints**	change in the composite achievement rate (TIR > 70% and TBR3.9 < 4%) at 1 month (Weeks 2–4) post-intervention
	Changes in glycemic parameters at Week 4 and Week 12 post-intervention
	Changes in pancreatic β-cell function at Week 4 and Week 12 post-intervention
	Changes in insulin sensitivity indicators at Week 4 and Week 12 post-intervention
	Changes in TDD at Week 4 and Week 12 post-intervention
	Changes in infection and inflammatory markers at Week 4 and Week 12 post-intervention
	Changes in Intestinal Barrier-Related Antibodies at Week 4 and Week 12 post-intervention
	Changes in cellular immune indicators at Week 4 and Week 12 post-intervention
	Changes in lipid profile at Week 4 and Week 12 post-intervention
	Changes in gut microbiota composition and abundance at Week 4 and Week 12 post-intervention
	Changes in serum metabolomic profiles at Week 12 post-intervention
	Changes in PROs at Week 4 and Week 12 post-intervention
**Feasibility endpoints**	Recruitment rate
	Retention rate
	Intervention adherence
	Acceptability
**Safety endpoints**	Number of adverse events and serious adverse events

**Note:** All changes in the above-mentioned indicators are relative to baseline values. Glycemic parameters: including HbA1c, FBG, MMT 2h PG and other CGM metrics [TIR, TBR3.9, TAR, GMI, GRI, CV]; Pancreatic β-cell function: Including FCP, MMT 2h CP, and the AUC of MMT 2h CP; Insulin sensitivity indicators: Including eGDR; Infection and inflammatory markers: Including WBC, PCT, ESR, hs-CRP, and inflammatory cytokines; Intestinal Barrier-Related Antibodies: Including Anti-LPS, Anti-Occludin Antibodies; Cellular immune indicators: Including peripheral blood Treg/Th17 ratio and islet-related autoantibodies [GADA, IA-2A, ICA]; Lipid profile: Including TC, TG, LDL-c, and HDL-c; Serum metabolomic profiles: Including bile acids [e.g., UDCA, TUDCA] and SCFAs; PROs: Including EQ-5D-5L, CHFSII-WS, and DDS; Recruitment rate: Proportion of screened participants enrolled; Retention rate: Proportion of participants completing the 12-week follow-up; Intervention adherence: Percentage of prescribed capsules consumed; Acceptability; Participant-reported tolerability and willingness to undergo treatment. Serious adverse events: Including severe hypoglycemia, diabetic ketoacidosis and severe allergic reactions;

**Abbreviations:** TIR, Time in Range; TBR3.9, Time Below Range <3.9 mmol/L; HbA1c, Glycated hemoglobin; FBG, Fasting Plasma Glucose; MMT 2h PG, 2-hour Postprandial Glucose during Mixed-Meal Tolerance Test; CGM, Continuous Glucose Monitoring; TAR, Time Above Range; GMI, Glucose Management Indicator; GRI, Glycemic Risk Index; CV, Coefficient of Variation; FCP, Fasting C-Peptide; MMT 2h CP, 2-hour Postprandial C-Peptide during Mixed-Meal Tolerance Test; AUC, Area Under the Curve; eGDR, Estimated Glucose Disposal Rate; TDD, Total daily insulin dose; WBC, White Blood Cell count; PCT, Procalcitonin; ESR, Erythrocyte Sedimentation Rate; hs-CRP, High-Sensitivity C-Reactive Protein; Anti-LPS, Anti-Lipopolysaccharide; Treg, Regulatory T cells; Th17, T helper 17 cells; GADA, Glutamic Acid Decarboxylase Antibody; IA-2A, Insulinoma-Associated Antigen-2 Antibody; ICA, Islet cell autoantibodies; TC, Total Cholesterol; TG, Triglycerides; LDL-c, Low-Density Lipoprotein Cholesterol; HDL-c, High-Density Lipoprotein Cholesterol; UDCA, Ursodeoxycholic Acid; TUDCA, Tauroursodeoxycholic Acid; SCFAs, Short-Chain Fatty Acids; PROs, patient-reported outcomes; EQ-5D-5L, EuroQol Five-Dimension Five-Level Questionnaire; CHFSII-WS, Chinese version of the Hypoglycemia Fear Survey II-Worry Scale; DDS, Diabetes Distress Scale;

### 2.6. Risk and AEs

An AE is defined as any unfavorable medical occurrence in an individual after signing the informed consent form and entering the study until the last follow-up, regardless of whether it had a causal relationship with yFMT capsules. The anticipated risks associated with the intervention include gastrointestinal symptoms (e.g., nausea, abdominal pain, diarrhea, bloating, constipation), fatigue, decreased appetite, and potential metabolic or immune-related complications (e.g., diabetic ketoacidosis, severe hypoglycemia, severe allergic reactions).

In the event of any AEs, the investigators will provide prompt management and may discontinue the study intervention based on the clinical judgment of the investigator. All AEs, regardless of severity, will be recorded in the case report form and followed until satisfactory resolution. Only SAEs are required to be reported to the Institutional Review Board as mandated by the protocol and regulatory guidelines.

### 2.7. Withdrawal standard

DMC will periodically convene to make clinical judgments on who should withdraw from the study. The following withdrawal rules will be abided by (1) SAEs; (2) failure to complete the yFMT intervention per protocol (e.g., missing ≥50% of the doses); (3) pregnancy or planned pregnancy; and (4) development of a newly diagnosed condition that met exclusion criteria (e.g., inflammatory bowel disease, malignancy) or any other situation in which the investigator determined that study discontinuation was warranted. It should be noted that participants maintain the right to terminate the study at any time without impact on future care.

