### 2.9. Sample size and pilot trial rationale

This is a pilot study. The primary objectives are to assess the feasibility (recruitment, adherence) and safety of the oral yFMT, to evaluate the preliminary effciency, and to collect preliminary effect-size estimates for the planning of a subsequent pivotal trial.

As no prior data exist on achieving the composite glycemic target (TIR > 70% with TBR3.9 < 4%) following yFMT in adults with T1DM, a traditional sample size calculation based on an anticipated effect size was not feasible. The sample size for this trial was therefore determined in accordance with methodological best practices for pilot trial design. We referenced the guidance proposed by Wang et al., which indicates that a pilot study for a future definitive trial with 90% power and a two-sided alpha of 0.05 typically requires approximately 10–25 participants per group to provide meaningful parameter estimates for small-to-moderate effect sizes [23]. Based on this, and considering the common requirement for assessing primary feasibility objectives (e.g., recruitment rate, procedural acceptance), a sample size of 10 participants per group was set.

A pre-planned interim analysis will be conducted after the first 10 participants (50% of the total planned sample) have completed the 12-week follow-up. During this interim analysis, the DMC will review unblinded data, including safety outcomes and the primary composite endpoint, to evaluate safety and obtain preliminary treatment effect estimates for future sample size planning. No formal hypothesis testing will be performed, and no sample size re-estimation is planned for the current trial, consistent with its pilot nature. Based on the DMC’s review, the trial may continue as planned, be modified, or be terminated early if unacceptable safety concerns or clear futility are observed.

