### 2.10. Statistics and analysis

Efficacy analyses will be performed in the intention-to-treat population. For the primary efficacy endpoint, participants with missing primary endpoint assessments will be considered non-responders using a non-responder imputation approach in the intention-to-treat analysis. Safety analyses will be performed in the safety analysis set. Normality of continuous variables will be assessed using the Shapiro-Wilk test at each time point. Normally distributed data will be presented as mean±standard deviation and analyzed using independent samples t-test (between-group) or paired t-test (within-group). Non-normally distributed data will be presented as median (Q1, Q3) and analyzed using Mann-Whitney U test (between-group) or Wilcoxon signed-rank test (within-group). Categorical data will be expressed as count (percentages) and analyzed using Fisher’s exact test.

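### Section 2.7 has the DMC judge which individuals withdraw, yet the same DMC sees unblinded primary results at the interim, so later exits may be decided with knowledge of results by arm

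*Protocol article*

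**What the plan says.** Four statements in the protocol article bear on this point.

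- **Who decides withdrawals (2.7).** "DMC will periodically convene to make clinical judgments on who should withdraw from the study". The section then lists grounds: serious adverse events, incomplete intervention, pregnancy or planned pregnancy, and a new excluding condition. Item 4 adds "any other situation in which the investigator determined that study discontinuation was warranted".
- **Who may see the code (2.4.3).** It is closed to investigators, participants and endpoint assessors, "except for authorized access by the independent Data Monitoring Committee (DMC) during the pre-specified interim analysis". An independent statistician keeps it.
- **What the DMC sees and may recommend (2.9).** Once the first 10 participants have completed 12 weeks, "the DMC will review unblinded data, including safety outcomes and the primary composite endpoint". The outcomes described are at trial level only: continue, modify or terminate.
- **What a missing endpoint becomes (2.10).** In the intention-to-treat analysis, "participants with missing primary endpoint assessments will be considered non-responders".

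Section 2.6 is related but separate. After an adverse event, investigators "may discontinue the study intervention based on the clinical judgment of the investigator". That concerns stopping the capsules, not leaving the study.

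**The concern.** A data monitoring committee can safely hold unblinded results because it normally advises on the trial as a whole and does not act on single participants. Section 2.7 removes that separation by giving the DMC repeated, judgment-based decisions about individuals. Once the committee has seen the primary endpoint by arm, it cannot set that knowledge aside at its next meeting.

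Withdrawal feeds directly into results. The primary endpoint rests on glucose monitoring in Weeks 10–12. A participant who leaves earlier and has no such data counts as a failure, and also counts against retention, which is a feasibility endpoint. Dosing lasts only six days, so for anyone past Day 6 a withdrawal from the study stops no capsules. Its effect is on follow-up.

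What is at stake is chiefly the estimated treatment effect, because section 2.9 gives the collection of effect-size estimates for a pivotal trial as one of the study's purposes.

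**Working it through.** **1. The plan's own figure.** Section 2.9 sets 10 per group and places the interim at 10 participants, stated as 50%. Check: 10 / (2 × 10) = 0.50, so the figure is reproduced. Participants who have not completed Week 12 at that point: 20 − 10 = 10. This is the most that can be exposed. The first 10 have finished, and before the interim the text gives the DMC no codes.

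**2. Who those 10 are, assuming even recruitment.** Section 2.2 gives 20 November 2025 to 31 July 2026, which is 253 days. The tenth participant enters at day 253 × 10/20 = 126.5.
- Adding 84 days (12 weeks): day 210.5, about 18 June 2026. Enrolled by then: 20 × 210.5/253 = 16.6.
- Adding 84 + 17 days (with the run-in): day 227.5, about 5 July 2026. Enrolled by then: 20 × 227.5/253 = 18.0.

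So about 7 or 8 participants would be in the study and unfinished, and the other 2 or 3 would still be to come.

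**3. Effect of one exit.**
- Primary endpoint: a would-be responder scored as a non-responder moves that arm's rate by 1/10 = 10 percentage points.
- Retention, defined in section 2.5 over participants as a whole: 1/20 = 5 points. The figure is 10 points only if retention is reported by arm.

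**4. Effect of an imbalance when the treatment does nothing.** Let p be the true response rate in both arms, and let k be the number of excess withdrawals in one arm, chosen without regard to outcome and scored as failures. The expected spurious difference is 100 × p × k/10 points. The rejection rate of the two-sided Fisher's exact test at 0.05 comes from exact binomial enumeration with 10 per arm. The documents give neither p nor k, so both are assumptions and are shown over a range.

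| k | Difference, p = 0.3 / 0.5 / 0.7 (points) | Fisher rejection, p = 0.3 / 0.5 / 0.7 |
|---|---|---|
| 0 | 0 / 0 / 0 | 1.19% / 1.28% / 1.19% |
| 1 | 3 / 5 / 7 | 1.16% / 1.28% / 1.25% |
| 2 | 6 / 10 / 14 | 1.31% / 1.75% / 2.28% |
| 3 | 9 / 15 / 21 | 1.64% / 2.69% / 4.20% |
| 5 | 15 / 25 / 35 | 2.96% / 6.70% / 13.24% |

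The row k = 5 is a bound and not a plausible case. It would remove about every unfinished participant in one arm (10 unfinished, about 5 per arm). For k up to 3 the test stays below 5%, while the estimate moves by as much as 21 points. The exposure is therefore in the estimate more than in the test.

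**The case against.** The strongest reply is that nothing shows the DMC learning the allocation of anyone it could still withdraw. Code access is limited to the interim, and that analysis concerns participants who have already finished. This stands in part. A reader might infer that the committee knows the arm of every unfinished participant, but the text does not say so. It leaves open whether access covers the whole list or only the first 10. Inferring later assignments from permuted blocks would need a block size, and none is stated. What is stated is that the committee sees the primary endpoint unblinded and goes on making individual judgments.

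Other replies also narrow the point:

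- **The DMC is not alone in handling codes.** "The randomization code will be securely maintained by an independent statistician throughout the study", and an independent researcher opens the envelopes. Neither has a stated role in withdrawals.
- **Most grounds are fairly objective.** Item 2, for example, is "failure to complete the yFMT intervention per protocol (e.g., missing ≥50% of the doses"), and doses are observed by nurses. The open-ended ground refers to the investigator, who is blinded. Discretion enters through the opening sentence, which calls the decisions clinical judgments.
- **The investigator's authority.** A reader might take section 2.6 as already giving the investigator study withdrawal. It does not, because it covers stopping the intervention. The tension over who decides withdrawal lies within section 2.7, between its opening sentence and item 4.
- **The double blind as a whole.** A reader might infer that it fails. It does not: participants, investigators and endpoint assessors stay blinded, and the glucose metrics are calculated by software.
- **A charter may separate open and closed sessions.** That may be so, and the absence of such detail from an article is no fault. The point here rests on what sections 2.7, 2.4.3 and 2.9 do say, which is that one body holds both roles.

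**Conclusion.** The point holds in limited form. The article assigns individual withdrawal judgments to the same committee that it unblinds at the interim, and section 2.9 otherwise describes that committee's role at trial level only. The exposure covers the up to 10 of 20 participants unfinished at the interim.

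Each would-be responder who is withdrawn and lacks Weeks 10–12 data shifts that arm's rate by 10 points, and each exit shifts overall retention by 5. With no true effect, two or three excess withdrawals in one arm would produce an expected difference of 6 to 21 points for response rates of 0.3 to 0.7. These counts and rates are illustrative assumptions. The documents give no basis for saying how likely an arm-related exit is or which arm it would favor. The result also depends on withdrawal leading to missing data.

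The documents do not support a claim that withdrawals will depend on arm, or that the false-positive rate is materially raised. They support the narrower conclusion that, as written, arm-level results could inform who leaves, and that a change of wording would prevent it.

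**What to change.** Reconcile sections 2.4.3, 2.7 and 2.9 on who takes participant-level withdrawal decisions and whether that party is blinded:

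- State in 2.7 that these decisions are made by a party blinded to allocation and to interim results. Item 4 already refers to the investigator's determination, so this fits the existing text.
- Require the reason for each withdrawal to be recorded before unblinding.
- Limit the DMC's unblinded role to safety review and the trial-level recommendations that 2.9 already describes.

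The withdrawal grounds themselves are left unchanged, as is the right of participants to leave.

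The cost is a wording amendment to a trial that has been recruiting since November 2025, with no added visits or participants. The small downside is that the DMC no longer decides single withdrawals, although it still reviews the safety data.

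### Section 2.7 withdraws participants from the study, not only from the capsules, so a protocol rule can create missing Week 12 outcomes that count as non-response and lower retention

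*Protocol article*

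**What the plan says.** Section 2.7 of the protocol article gives the decision to the data monitoring committee: "DMC will periodically convene to make clinical judgments on who should withdraw from the study". It continues: "The following withdrawal rules will be abided by (1) SAEs; (2) failure to complete the yFMT intervention per protocol (e.g., missing ≥50% of the doses". Pregnancy, newly diagnosed excluded conditions and a catch-all follow. The catch-all is also worded as leaving the study: "any other situation in which the investigator determined that study discontinuation was warranted".

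Section 2.6 uses a different concept. After an adverse event the investigator "may discontinue the study intervention based on the clinical judgment of the investigator". It adds: "All AEs, regardless of severity, will be recorded in the case report form and followed until satisfactory resolution".

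Section 2.10 analyses efficacy by intention to treat, and "participants with missing primary endpoint assessments will be considered non-responders using a non-responder imputation approach in the intention-to-treat analysis".

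Other sections supply the context:
- **Section 2.4.4:** capsules are taken for six consecutive days.
- **Section 2.5:** the primary endpoint is read from CGM in Weeks 10–12. Retention is the share of participants who complete 12 weeks. SAEs include severe hypoglycemia, ketoacidosis and hospitalization.
- **Table 2:** liver, renal and thyroid function are scheduled at baseline and Week 12 only.

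**The concern.** Stopping a treatment and leaving a trial are different events, and section 2.7 treats a reason for the first as a reason for the second. Once the six-day course is over, withdrawal has no study treatment left to stop. Its only effect on the trial is to remove observations that could have been made.

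The missing value is then scored as failure. Because the listed SAEs include glycemic events and the other trigger reflects tolerability, the missingness is plausibly related to outcome and could be unequal between arms. The same decision also lowers retention, which is a feasibility endpoint in a trial whose first stated objectives in section 2.9 are feasibility and safety. The effect estimate and the retention rate are both meant to inform the next trial, so both would partly reflect the rule rather than the treatment or the participants' willingness to stay.

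**Working it through.** **Reading the sections together**
1. Section 2.7 leads to withdrawal from the study. No section says that a withdrawn participant continues to the Week 4 or Week 12 visit or wears CGM again.
2. An SAE in Week 8, for example, falls well after the last capsule. Withdrawal then means no Weeks 10–12 CGM and no scheduled post-treatment liver, renal or thyroid result, because Week 12 is the only planned one.
3. Section 2.10 scores the missing primary endpoint as non-response, and section 2.5 counts the participant as not retained.

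**Inputs**
- 10 per group, 2 × 10 = 20 in total (section 2.9).
- The article gives no expected withdrawal rate, achievement rate or dropout allowance. The sample size comes from pilot guidance of 10–25 per group, so there is no figure of the plan's own to reproduce. Rates marked *assumed* are mine.

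**Effect of each withdrawal**
- Arm achievement rate: 1/10 = 10 points if the participant would have met the target, and 0 if not. Two such participants in one arm: 20 points.
- Overall retention: 19/20 = 95% after one withdrawal and 18/20 = 90% after two. Retention within the arm: 9/10 = 90% and 8/10 = 80%.

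**Unequal withdrawal with no true effect** (*assumed* rates)

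Let p be the true achievement rate in both arms and w the withdrawal proportion, with withdrawal independent of achievement within each arm. The expected observed rate is p × (1 − w), so the expected spurious difference (yFMT minus placebo) is p × (w_placebo − w_yFMT).

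| Withdrawal, yFMT v placebo | p = 0.3 | p = 0.5 | p = 0.7 |
|---|---|---|---|
| 10% v 0% | −3 points | −5 points | −7 points |
| 20% v 0% | −6 points | −10 points | −14 points |

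The sign reverses if placebo loses more. If those withdrawn are less likely than average to be achievers, the shift is smaller.

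**Chance that the rule operates at all** (*assumed* per-person risk q)

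P(at least one of 20) = 1 − (1 − q)^20, which gives 33%, 64%, 88% and 96% for q = 2%, 5%, 10% and 15%.

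**Illustration with Fisher's test** (the sensitivity analysis in section 2.10)
- 5/10 v 0/10: p = 2 × 252/15504 = 0.0325.
- 4/10 v 0/10, after one achiever is withdrawn: p = 2 × 210/4845 = 0.087.

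These counts are hypothetical, and the primary model is a GEE. They show only how much one participant weighs.

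**The case against.** Several stronger readings are tempting, and the document does not support them.

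- **Every SAE forces withdrawal.** The list of SAEs is unqualified, but the sentence before it makes withdrawal a matter of clinical judgment, so it is not automatic. The dose threshold is an example of failure to complete, and dosing is directly observed by nurses (section 2.4.7), so that trigger may be rare.
- **The rule contradicts intention to treat.** It does not. Imputation keeps withdrawn participants in the analysis set. What is lost is an observed outcome, replaced by an assumed one.
- **Safety follow-up ends.** Section 2.6 follows adverse events to resolution. Only the scheduled assessments are at risk.
- **The unblinded committee can withdraw people by allocation.** Section 2.4.3 keeps the code closed "except for authorized access by the independent Data Monitoring Committee (DMC) during the pre-specified interim analysis", and that analysis comes after the first 10 participants have finished. Nothing says the committee sees later participants' allocations, so this is speculation.

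Three further objections deserve an answer. First, counting severe hypoglycemia or ketoacidosis as failure of a glycemic target can be a defensible composite strategy. That is true, but section 2.10 bases failure on a missing assessment and does not define those events as failure. The rule also reaches hospitalization for any cause and incomplete dosing.

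Second, in a trial of 20 any loss has this weight, and earlier FMT studies are described as generally safe. That stands as a limit on likelihood. These losses, however, would be made by the protocol and are avoidable.

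Third, a condensed article may leave data collection after withdrawal to the full protocol. That absence is not the finding. The finding rests on what 2.7 states: withdrawal from the study on grounds that need only concern the intervention.

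**Conclusion.** The concern holds as a fault in how sections 2.6, 2.7 and 2.10 fit together. Followed as written, section 2.7 can turn an observable Week 12 outcome into an imputed failure and lower retention by decision of the trial. The size is up to 10 percentage points on an arm's achievement rate and 5 points on overall retention per withdrawal. This assumes that withdrawal from the study ends scheduled visits and CGM, which is the plain reading.

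Non-responder imputation is not itself the error. Bias in the treatment contrast is possible but not demonstrated: it needs withdrawals that differ by arm, or that fall unequally on would-be achievers, and the article gives no rates from which to judge either.

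**What to change.** Amend section 2.7, and align 2.6 and 2.10 with it, so that the text:

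1. distinguishes discontinuing the capsules from leaving the study;
2. states that a participant who meets a 2.7 criterion continues the already scheduled Week 4 and Week 12 data collection, where the participant consents and the investigator considers it appropriate;
3. states that observed Week 12 data are used in the intention-to-treat analysis, with non-responder imputation kept for values that are truly missing;
4. reports retention with rule-driven withdrawals shown separately from participant-initiated ones.

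The clinical criteria for stopping, and who judges them, need not change for this purpose. With retained follow-up, the missing data due to the rule fall to those cases where continuation is declined or judged inappropriate. The sample size stays at 10 per group.

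The cost is a short amendment and a few more follow-up visits than the current rule would produce. Those visits are already in the schedule. Recruitment has been open since November 20, 2025, so the change is best made soon: Week 12 data that are not collected cannot be recovered.
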